### 2.7 Statistical analysis

#### 2.7.1 Sample size.

Our study is a noninferiority study. With a bilateral α = 0.05, a test efficacy of 1-β = 80%, a 3-year disease-free survival rate of 75%, and a noninferiority threshold of 20%, the estimated minimum sample size for each group is 74. Considering a dropout rate of 20% (according to EMEA [26], ICH [27], and FDA [28] guidelines and previous studies [29]), we ultimately decided to include 100 patients in each group, totaling 200 patients across both groups.

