#### 2.7.3 Statistical methods.

Local recurrence is defined as tumor recurrence in the lumen or in the mesorectum and must be confirmed by a pathological biopsy. A distant metastasis is defined as a metastasis that is discovered in the liver, lung, bone, or other sites by CT, MRI, or radionuclide scanning, with or without pathological examination. Disease-free survival (DFS) is defined as the absence of local recurrence, distant metastasis, and death from any cause. Overall survival (OS) is defined as the absence of death from any cause. The duration of follow-up will be calculated from the date of surgery to the event of interest or the last follow-up date.

To determine the consistency between the PTC drug sensitivity results and clinical outcomes, the following methods will be employed (Table 2): positive consistency rate = a/(a + c) × 100%; negative consistency rate = d/(b + d) × 100%; overall consistency rate = (a + d)/(T1) × 100%; sensitivity = a/(a + b) × 100%; and specificity = d/(b + d) × 100%.

**Table 2 pone.0326760.t002:** Consistency test of recurrence and metastasis cases.

Drug sensitivity test	Clinical efficacy		Sum
	CR + PR	SD + PD	
**Effective**	a	B	a + b
**Invalid**	c	D	c + d
**Sum**	a + c	b + d	T1

The results will be presented as median values or means ± standard deviations for continuous variables and as numbers (percentages) for categorical variables. The t test and Wilcoxon rank sum test will be used to compare continuous variables, and chi-square analysis/Fisher’s exact test will be used to compare categorical variables. Survival analysis will be conducted using the Kaplan-Meier curves. Log-rank test to compare the primary endpoint between different arms in the presence of censoring. A P value of 0.05 or less is considered statistically significant. All the statistical tests will be two-sided. All analyses will be performed using SPSS Version 26.0 (SPSS Inc., Chicago, IL).

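### The trial is sized for noninferiority, but the only primary test named is a two-sided log-rank test of no difference that never uses the margin

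*Protocol article*

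**What the plan says.** Section 2.7.1 (Sample size) is explicit about the design: "Our study is a noninferiority study". It sets two-sided alpha at 0.05, power at 80%, 3-year DFS at 75% and the noninferiority threshold at 20%, and concludes that "the estimated minimum sample size for each group is 74". A 20% dropout allowance then takes this to 100 per group.

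Section 2.6 (Follow-up and endpoints) makes the 3-year DFS rate the main endpoint, with follow-up to five years.

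Section 2.7.3 (Statistical methods) names the primary comparison: "Log-rank test to compare the primary endpoint between different arms in the presence of censoring". It takes P of 0.05 or less as significant and adds: "All the statistical tests will be two-sided". Kaplan-Meier curves are mentioned, but no interval for the 3-year rate or its difference. The other tests listed (t, Wilcoxon, chi-square, Fisher) are general and are also tests of no difference.

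The 20% threshold appears only in the sample-size paragraph. Nowhere is a confidence limit or test statistic compared with it.

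**The concern.** A noninferiority trial must reject the hypothesis that the new strategy is worse than control by at least the margin. The log-rank test at P ≤ 0.05 rejects a different hypothesis, that the two survival curves are the same. Three consequences follow.

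- A nonsignificant log-rank result is not evidence of noninferiority, and a significant one is not needed for it.
- The stated 80% power does not belong to the test that is named.
- The log-rank test compares whole curves, while the endpoint is a rate at 3 years. Section 2.7.3 does not say whether the data are cut at 3 years or run on to 5.

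With the rule as written, two outcomes are likely. If the arms are equal, as the sample size assumes, the primary test will almost never be significant and the trial misses its own hypothesis. Alternatively, P > 0.05 is read as noninferior, a claim whose error rate the plan does not control. Either way, the conclusion on the primary endpoint would rest on a rule chosen after the data are seen.

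**Working it through.** **Inputs from section 2.7.1:** two-sided alpha 0.05 (one-sided 0.025 for the lower limit), power 80%, 3-year DFS 75%, margin 20%, 74 per group before dropout and 100 after.

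**Assumptions:** only one DFS rate is given, so it is taken as the true rate in both arms. The margin is read as 20 percentage points. Both readings are supported because together they reproduce the stated 74.

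**Step 1. Reproduce the plan's figure.**

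n = (1.960 + 0.842)² × 2 × 0.75 × 0.25 / 0.20² = 73.6, so 74 per arm.

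This is the formula for noninferiority on a difference in proportions. Alternatives do not give 74:
- one-sided 0.05 gives 58;
- a two-proportion test of difference gives 89 for 75% v 55% and 49 for 75% v 95%.

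Dropout: 74 / 0.8 = 92.5, so 93; 100 per group covers it.

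**Step 2. Power of the matching rule.** The rule is that the lower 95% limit for the difference (PTC-guided minus control) lies above −20 points. With equal arms at 75%, SE = √(2 × 0.75 × 0.25 / n) and power = Φ(0.20/SE − 1.96).

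| n per arm | SE | Power |
|---|---|---|
| 74 | 0.0712 | 80.2% |
| 80 (100 less 20%) | 0.0685 | 83.2% |
| 100 | 0.0612 | 90.4% |

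**Step 3. Power of the named test.** With equal arms, a two-sided log-rank test at 0.05 is significant about 5% of the time by construction, and about 2.5% of the time in favour of the PTC-guided arm.

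If the PTC-guided arm is truly better, take exponential DFS, HR = ln(S_PTC)/ln(0.75), events = n × (0.25 + 1 − S_PTC), and power = Φ(√(events/4) × |ln HR| − 1.96):

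| True 3-year DFS, PTC v control | HR | Power, 80 per arm | Power, 100 per arm |
|---|---|---|---|
| 80% v 75% | 0.776 | 11.5% | 13.4% |
| 85% v 75% | 0.565 | 36.5% | 43.9% |
| 90% v 75% | 0.366 | 75.7% | 84.4% |

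Power near 80% therefore needs a true rate near 90% in the PTC-guided arm, which the protocol does not assume.

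**Step 4. Compare the two rules by simulation.** Settings: exponential DFS, 100 per arm, 20% uniform dropout, censoring at 3 years, 6,000 runs.

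| True 3-year DFS, control v PTC | Log-rank P > 0.05 | Interval rule met |
|---|---|---|
| 75% v 75% | about 95% | 87% |
| 75% v 65% | 69% | 32% |
| 75% v 55% (at the margin) | 17% | 2.3% |

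Repeat simulations under the same settings gave 68 to 69% against 30 to 32% in the second row, and 18 to 19% against 2.3 to 3% in the third.

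**Step 5. Size of the error if nonsignificance is read as noninferiority.** At the margin, 17 / 2.3 ≈ 7, so false claims rise about sevenfold. The formula in step 3 agrees in order of size. For 55% v 75%, HR = ln(0.55)/ln(0.75) = 2.08. At 80 per arm, events = 80 × 0.70 = 56, and the log-rank test misses the loss in 22% of trials. At 100 per arm (70 events) it misses it in 14%.

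**The case against.** The strongest counter-argument is that the log-rank test may be the intended analysis and the sample-size paragraph the misfit. The abstract, section 2.1 and the Discussion speak of improving outcomes and increasing survival benefit, which is the language of superiority. On that reading the two-sided log-rank test fits, and the sample size is the weak part: with 100 per arm and dropout, simulated log-rank power is 38% for 85% v 75% and 76% for 90% v 75%. These are general aims, however. They do not displace an explicit declaration of noninferiority, a stated margin and a sample size derived from it.

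Several narrower points are fair and limit the claim:

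- The article does not call the log-rank test a superiority test. It is a test of no difference.
- A significant result favouring the PTC-guided arm would in practice also support noninferiority. Under the design assumption this happens in about 2.5% of trials.
- The 80% power is correct for the noninferiority comparison. The fault is that this comparison is not the one named.
- The article never says that P > 0.05 will be read as noninferiority, so the sevenfold figure is a conditional risk.
- The simulations stop at 3 years and so do not quantify the effect of using 5-year curves.

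It could also be said that a condensed article leaves the decision rule to the analysis plan. That would answer silence, but section 2.7.3 names the primary test and its criterion, and an analysis plan faithful to it would carry the mismatch forward.

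**Conclusion.** The concern holds. Sections 2.7.1 and 2.7.3 contradict each other on the primary hypothesis, and as written the trial has no rule by which it could declare noninferiority. The sample size of 74, raised to 100 per group, is right for the declared design and needs no change.

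Under the design's own assumption, the named test is significant in about 5% of trials, whereas the matching interval rule succeeds in 80% at 74 per arm and about 87% at 100 per arm with dropout. If nonsignificance were taken as noninferiority, a full 20-point loss would be accepted in about 17 to 19% of trials instead of about 2.5%.

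These figures rest on equal true rates of 75% for the power statements, a margin in absolute percentage points, exponential DFS, and 20% uniform dropout in the simulations. The mismatch itself depends on none of them. Because it concerns the decision rule for the primary endpoint, it must be fixed before any outcome data are compared.

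**What to change.** State the primary analysis in section 2.7.3, and in the analysis plan, along these lines:

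> The primary analysis estimates the difference in Kaplan-Meier 3-year DFS, PTC-guided minus control, with a two-sided 95% confidence interval based on Greenwood variances. Noninferiority is declared only if the lower limit is above −20 percentage points. The log-rank test is supportive. A log-rank P value above 0.05 is not evidence of noninferiority.

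In formula: lower limit = [S_PTC(3) − S_control(3)] − 1.96 × √(Var_PTC + Var_control), to be compared with −0.20.

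Say also that the margin is an absolute difference, and bring the statements of aim in the abstract, section 2.1 and the Discussion into line with the noninferiority objective. If superiority is to be claimed as well, describe it as a further test once noninferiority is shown.

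The cost is a few sentences of protocol and analysis-plan wording, with the same data and no extra patients. The article reports all sites still open to recruitment at publication, so the rule can be fixed before results are known. Only if the sponsor decided that superiority is the true objective would the cost be larger, because the sample size would then have to be re-derived.

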**Methods and design:**

This multicenter randomized controlled trial (RCT) aims to evaluate the consistency between the in vitro PTC drug sensitivity test results with whole exome sequencing and the clinical prognosis of CRC patients. The study will involve 200 patients who will be randomly assigned to receive either PTC-guided adjuvant chemotherapy or traditional chemotherapy. The primary endpoint is the 3-year disease-free survival rate (3yDFS), with secondary endpoints including the consistency between test results and clinical outcomes and the prognostic value of gene mutations and other biomarkers.

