#### 2.5.2 Whole-exome gene sequencing (WES).

We will perform whole-exome gene testing on the patient’s histological specimens. The specific testing procedure is as follows: 1) tumor-targeted genes, including point mutation, insertion/deletion, fusion, and copy number variation analyses, will be used to predict the effectiveness of targeted drugs, tumor molecular subtypes, and patient prognosis; 2) a total of 145 tumor chemotherapy-related genes will be used to predict the effectiveness and side effects of commonly used chemotherapy drugs; 3) tumor mutational burden and microsatellite instability will be used to predict the efficacy of immunotherapy drugs; and 4) tumor susceptibility genes will be used to predict the genetic risk of multiple tumors.

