### 2.6 Follow-up and endpoints

The patient’s age, sex, pathological type, treatment plan, treatment drug dosage and cycle, pretreatment clinical staging, imaging results, oncological outcomes, etc., will be recorded. After discharge, patients will be reexamined in the outpatient clinic two to three weeks postsurgery to record any short-term complications and will subsequently be followed up for five years. Within the first two years postsurgery, patients will undergo clinical examinations every three months, including a digital rectal examination (DRE), examination of tumor markers such as CEA and CA19−9, chest X-ray (front and side views), and abdominal ultrasound (liver, gallbladder, pancreas, spleen, and kidney). Within two to three years postsurgery, patients will be followed up every six months. After three years, annual follow-ups will be conducted, which will include chest–abdomen–pelvis enhanced CT scans, rectal MRI or rectal ultrasound, and colonoscopy.

Follow-up will be conducted through doctor outpatient reviews as well as specialized follow-up personnel via phone, e-mail, text and other means. During the follow-up process, detailed records of the patient’s status (tumor-free survival, local recurrence, distant metastasis, death, etc.) will be recorded. The time, location, and cause of the endpoint event will also be recorded.

The main endpoint of the study is the 3yDFS rate. The secondary endpoints of the study are as follows: 1) consistency between the test results of the extended medication regimen and the clinical outcomes; 2) time to progression (TTP), objective response rate (ORR), progression-free survival (PFS), and overall survival (OS); and 3) consistency of gene mutation status, tumor mutation burden (TMB), microsatellite instability (MSI), and mismatch repair (MMR) status with clinical prognosis.

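### The blanket two-sided 0.05 rule also covers the genomic secondary endpoint, with the number of tests left open, so false 'significant' markers are inflated, and likely in a broad gene-by-gene screen

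*Protocol article*

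**What the plan says.** Section 2.7.3 of the protocol article gives one decision rule: "A P value of 0.05 or less is considered statistically significant". It continues: "All the statistical tests will be two-sided". No endpoint is excepted from either sentence.

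Section 2.6 names 3-year DFS as the main endpoint. The second group of secondary endpoints is TTP, ORR, PFS and OS. The third is "consistency of gene mutation status, tumor mutation burden (TMB), microsatellite instability (MSI), and mismatch repair (MMR) status with clinical prognosis". The abstract describes the same item as "the prognostic value of gene mutations and other biomarkers".

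Section 2.4 has both arms undergo whole-exome sequencing. Section 2.5.2 sets out its uses. Tumor-targeted genes, whose number is not stated, "will be used to predict the effectiveness of targeted drugs, tumor molecular subtypes, and patient prognosis". Separately, "a total of 145 tumor chemotherapy-related genes will be used to predict the effectiveness and side effects of commonly used chemotherapy drugs".

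The article does not call any of these analyses exploratory. It does not say how many genes will be related to prognosis, or by which test.

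**The concern.** A 0.05 threshold limits the error of one test. Applied without qualification to a family of markers, it lets the chance of at least one false declaration grow with the size of the family, and here the size is left open. The data source is a whole exome, so the family could be large.

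The abstract lists prognostic value of mutations and biomarkers among the secondary results. A reader of the eventual report would take a gene called statistically significant as a finding of a randomized trial. Under the rule as written, that label needs only one unadjusted P value of 0.05 or less, however many genes were examined. The same threshold also applies, on its face, to any test of TTP, ORR, PFS or OS.

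**Working it through.** **Inputs from the article.** Per-test level 0.05, two-sided (2.7.3). Planned patients 200, all sequenced (2.4). 3-year DFS 75%, noninferiority margin 20 points, power 80% (2.7.1). Fisher's exact test is among the tests named for categorical variables (2.7.3).

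**Assumptions.** The family size m and the correlation between tests are not stated. I take m = 4 (one gene status plus TMB, MSI and MMR, the smallest reading), m = 20 (a short panel) and m = 148 (145 + 3, as if the 145 chemotherapy-related genes were all tested against prognosis, which the article does not say). All markers are taken as truly unrelated to prognosis.

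**The plan's own figure first.** Sample size per group = 2 × 0.75 × 0.25 × (1.960 + 0.842)² / 0.20² = 73.6, rounded up to 74, as stated. The sample size rests on two-sided 0.05 for the primary endpoint only and does not depend on the secondary analyses.

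**Independent tests at exactly 0.05.** The chance of at least one false positive is 1 − 0.95^m, and the expected number is 0.05 × m.

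**Correlated tests.** With a common correlation ρ and shared factor u, the chance is 1 − ∫ φ(u) [Φ((1.96 − √ρ·u)/√(1−ρ)) − Φ((−1.96 − √ρ·u)/√(1−ρ))]^m du.

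| m | Expected false positives | Independent | ρ = 0.5 | ρ = 0.9 |
|---|---|---|---|---|
| 4 | 0.2 | 0.19 | 0.16 | 0.09 |
| 20 | 1.0 | 0.64 | 0.42 | 0.16 |
| 148 | 7.4 | 0.999 | 0.85 | 0.24 |

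**How many tests would make an error nearly certain?** Solving 1 − 0.95^m = 0.95 gives m = ln 0.05 / ln 0.95 = 58.4, so 59 independent tests; for 0.99, 90.

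**Conservative exact test.** Take 50 events in 200 patients (25%, the complement of the planned 75%) and an assumed mutation prevalence of 5%, so 10 carriers. Fisher's test then rejects at 0.05 with true probability 0.017 under the null. For independent tests the family rates are:
- m = 4: 1 − (1 − 0.0171)^4 = 0.067
- m = 20: 1 − (1 − 0.0171)^20 = 0.29
- m = 145: 1 − (1 − 0.0171)^145 = 0.92, with 145 × 0.0171 = 2.5 false positives expected

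This reduction depends on prevalence: the same test at 20% prevalence has size 0.043, and 20 tests give 0.58.

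**The case against.** The strongest objection is that this is an omission and not an error. Multiplicity for secondary and biomarker endpoints commonly sits in a statistical analysis plan, which is not shown here, and a condensed article need not repeat it. The threshold sentence is also generic, and a Benjamini-Hochberg adjusted P value of 0.05 or less would satisfy it. This stands in part: the absence of a multiplicity procedure is no finding by itself. What remains is the rule that the article does state. It is unqualified, it covers the genomic endpoint, and followed literally it calls raw P values significant.

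Second, no gene-by-gene test is specified. The endpoint is worded as consistency; the one consistency method described (Table 2, for the PTC results) consists of descriptive percentages, and the log-rank test is named only for the primary endpoint. This stands as a limit on size. Part of the endpoint may be reported without P values, and the article does not say that TTP, ORR, PFS and OS will each be tested between arms.

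Third, a reader might infer that the 145 genes form the prognosis family, and hence that false prognostic genes are nearly certain. The article does not support this. Section 2.5.2 assigns those genes to drug effectiveness and side effects; the genes it ties to prognosis have no stated count. Near certainty would need about 59 or more nearly independent tests at full size, and correlation or rare mutations would lower the figure further.

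Finally, the guideline remark in the Discussion concerns PTC-guided treatment, not a list of genes, so it adds nothing to the stakes here.

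**Conclusion.** The point holds in a limited form. The article fixes one two-sided 0.05 rule for all tests, and that rule reaches a genomic secondary endpoint of unstated size. If no marker is related to prognosis, the chance of at least one false significant marker is about 0.09 to 0.19 with 4 tests, 0.16 to 0.64 with 20 and 0.24 to 0.999 with 148, each range running from correlation 0.9 to independence. With Fisher's exact test, 5% prevalence and 50 events in 200 patients, the independent figures fall to about 0.29 for 20 tests and 0.92 for 145.

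Error is above 0.05 in every case computed and probable in a broad gene-by-gene screen. The size depends on assumed test counts, correlations and mutation prevalence, and on P values actually being computed marker by marker. The matter is confined to secondary endpoints; the primary comparison and the 74 per group are not touched.

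**What to change.** In 2.7.3, state that the 0.05 rule does not apply to the third secondary endpoint. For that endpoint, report the number of genes and markers tested, declare a marker only under Benjamini-Hochberg control at a 5% false-discovery rate over all of them, and label the results exploratory. Report TTP, ORR, PFS and OS as supportive estimates with 95% confidence intervals and no claim of significance. A testing hierarchy among these four is not needed; one that starts with OS would be a debatable preference.

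This should not be worded as keeping the 0.05 rule for the primary comparison alone. The article declares a noninferiority aim, and a log-rank P value against 0.05 does not test the 20-point margin; that wording needs its own treatment.

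The cost is a few sentences, with no new patients or data. The downside is that fewer individual genes can be called significant. The sample size is unaffected.

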### 2.8 Quality control

To ensure that the quality of research activities meets the requirements, monitoring will be carried out at each stage of data processing to ensure that all the data are trustworthy and processed correctly. The sponsor is responsible for comprehensive tracking and monitoring of the implementation of clinical trials, ensuring that the experiments comply with relevant regulatory requirements and follow the experimental protocol. Clinical trial researchers are familiar with necessary regulatory requirements, possess professional expertise related to clinical trials, have the ability to design and implement relevant clinical trials, are familiar with relevant testing techniques, can correctly interpret test results, have passed qualification review, and are relatively fixed personnel. Laboratory quality control includes establishing unified laboratory standard operating procedures and quality control procedures and conducting quality control simultaneously during drug sensitivity testing. Only when the quality control results are qualified can the data be determined to be valid. The person in charge of statistics has a relevant professional background and abilities.

A double data check will also be performed for quality control. In accordance with the data collection methods and criteria developed by the project leader and professionals, all the data will be recorded carefully and comprehensively to ensure the authenticity of the data. Missing data from withdrawn participants will be imputed via the multiple imputation method.

### 2.9 Ethics and dissemination

All the subjects will participate in the study voluntarily, and the senior researchers on our project team, [name], [name], [name], [name], [name], [name], [name], and [name], will obtain written consent forms from each individual prior to their enrollment in the study. Both groups of subjects are expected to benefit from the study. Additionally, we will inform all the participants about any new information that may influence their willingness to participate in the study. The trial adheres to the criteria and principles outlined in the Declaration of Helsinki and received approval from the Ethics Committee of Peking Union Medical College Hospital (project ID: HS-3174B). This study will be subject to an annual ethical review. Furthermore, we registered the trial on chictr.org.cn. Any modifications to the study will be promptly communicated to the Ethics Committee of Peking Union Medical College Hospital and will be updated on the registration website once approval is obtained.

As the Chinese Clinical Trial Registry still allowed delayed registration after study began on 2021, we initiated recruitment after obtaining ethical approval. Sometime later, we realized that ClinicalTrials encourages authors to register before recruitment. Thus, we conducted a supplementary registration immedatly, which led to the trial being registered after patient recruitment had begun. We understand the importance of timely registration for the transparency, ethics, and credibility of research results, and we also recognize the potential impact of this delay. The authors confirm that all ongoing and related trials for this drug/intervention are registered.The entirety of the research-related data, including original data and records, quality control files, and software used for data storage and follow-up analysis, will be limited to access by the study team only. The statistical analysis and processing of the collected data will be conducted exclusively by designated researchers. The identity and contact information of all participants will be strictly confidential. Prior to performing the statistical analysis, the data will be anonymized. Ultimately, the research findings will be published in reputable scientific journals.

